**Figure 2 figure2:**
[figure not shown]
Exergame Device used as means to implement the “Brain-IT” training concept in this study: “Senso Flex” for home-based use (left side) and its stationary version (“Senso” for stationary use in physiotherapies, nursing homes, or rehabilitation clinics (right side). Photos provided by Dividat AG.

### Outcomes

#### Overview

To ensure comparability of the study outcomes, global cognitive functioning will be assessed as the primary outcome. As secondary outcomes, domain-specific assessments evaluating the key neurocognitive domains (as defined in [10] in line with DSM-V [12] and according to recommendations [7]) of (1) learning and memory; (2) complex attention; (3) executive function; and (4) visuospatial skills, as well as brain structure and function, spatiotemporal parameters of gait, IADL, psychosocial factors (ie, QoL, and levels of depression, anxiety, and stress), and cardiac vagal modulation (resting vm-HRV) will be assessed. Table 2 provides an overview of all endpoints.

**Table 2 table2:** Overview of all primary and secondary outcome measures, outcome variables and interpretation guide.

Outcome measures			Outcome variables		Interpretation guide
**Primary**					
[figure not shown]			Global cognitive functioning		
	Quick mild cognitive impairment screen [96,99]	Total point score		Improvement=↑^a^	
**Secondary**					
[figure not shown]			Learning and memory		
	Subtest “logical memory” of the Wechsler Memory Scale—fourth edition [100,101]	Total point score part 1—free recall		Improvement=↑	
	Subtest “logical memory” of the Wechsler Memory Scale—fourth edition [100,101]	Total point score part 2—free recall		Improvement=↑	
	Subtest “logical memory” of the Wechsler Memory Scale—fourth edition [100,101]	Total point score part 2—recognition		Improvement=↑	
	PEBL^b^ digit span forward [102-104]	Total point score		Improvement=↑	
	PEBL digit span forward [102-104]	Maximum span		Improvement=↑	
[figure not shown]			Complex attention		
	PEBL trail making test—part A [102]	Completion times		Improvement=↓^c^	
	PEBL trail making test—part A [102]	Number of errors		Improvement=↓	
	Subtest “Go-NoGo” of the test of attentional performance [105]	Median reaction time (ms)		Improvement=↓	
	Subtest “Go-NoGo” of the test of attentional performance [105]	Number of errors		Improvement=↓	
[figure not shown]			Executive function		
	HOTAP picture-sorting test part A [106]	Combi score (ie, sum of the points divided by the time they needed to arrange the cards) (points×min^−1^)		Improvement=↑	
	PEBL digit span backward [102-104]	Total point score		Improvement=↑	
	PEBL digit span backward [102-104]	Maximum span		Improvement=↑	
	PEBL trail making test—part B [102,104]	Completion time (s)		Improvement=↓	
	PEBL trail making test—part B [102,104]	Number of errors		Improvement=↓	
[figure not shown]			Visuospatial skills		
	PEBL-Mental Rotation Task [102,104,107]	Median reaction time of correct answered trials (ms)		Improvement=↓	
	PEBL-Mental Rotation Task [102,104,107]	Performance (number of correct answered trials)		Improvement=↑	
[figure not shown]			Brain Structure and Function		
	3D isotropic T1-weighted MRI^d^ scan	Gray matter volume of defined key regions of interest (mm^3^)		Improvement=↑	
	3D isotropic T1-weighted MRI scan	White matter volume of defined key regions of interest (mm^3^)		Improvement=↑	
	Diffusion Tensor Imaging MRI scan	Mean diffusivity of defined key regions of interest		Improvement=↓	
	Diffusion Tensor Imaging MRI scan	Fractional anisotropy of defined key regions of interest		Improvement=↑	
	Resting state T*2-weighted blood oxygen level-dependent fMRI^e^	Individual functional connectivity maps between the hippocampal seed and the defined key regions of interest		Improvement=↑	
	Task-based T*2-weighted blood oxygen level-dependent fMRI	Individual functional connectivity maps between the hippocampal seed and the defined key regions of interest		Improvement=↑	
[figure not shown]			Spatiotemporal parameters of gait		
	Gait analysis^f^ [108]	Walking speed (m/s)		Improvement=↑	
	Gait analysis	Stride duration (ms)		Improvement=↓	
	Gait analysis	Stride length (cm)		Improvement=↑	
	Gait analysis	Stance phase duration (ms)		Improvement=↓	
	Gait analysis	Swing time (ms)		Improvement=↓	
	Gait analysis	Single support time (ms)		Improvement=↓	
	Gait analysis	Double support time (ms)		Improvement=↓	
[figure not shown]			IADL^g^		
	Amsterdam IADL questionnaire [109]	T- score		Improvement=↑	
[figure not shown]			Psychosocial factors		
	Quality of life-Alzheimer disease [110-112]	Overall score		Improvement=↑	
	Depression, anxiety and stress scale-21 [113-117]	Overall score—subscale depression		Improvement=↓	
	Depression, anxiety and stress scale-21 [113-117]	Overall score—subscale anxiety		Improvement=↓	
	Depression, anxiety and stress scale-21 [113-117]	Overall score—subscale stress		Improvement=↓	
[figure not shown]			Resting vagally–mediated Heart Rate Variability		
	resting vm-HRV^h^ measurement^i^ [118]	Mean R-R time interval (ms)		Improvement=↑	
	Resting vm-HRV measurement	Root Mean Square of successive RR interval differences		Improvement=↑	
	Resting vm-HRV measurement	Percentage of successive RR intervals that differ by more than 50 ms (%)		Improvement=↑	
	Resting vm-HRV measurement	Absolute power of the high-frequency (0.15-0.4 Hz) band (ms^2^)		Improvement=↑	
	Resting vm-HRV measurement	Relative power of the high-frequency (0.15-0.4 Hz) band (nu)		Improvement=↑	
	Resting vm-HRV measurement	Poincaré plot SD perpendicular to the line of identity (ms)		Improvement=↑	
	Resting vm-HRV measurement	Parasympathetic nervous system tone index		Improvement=↑	

^a^Higher values or an increase over time indicate better functioning or improvement in the respective study endpoint.

^b^PEBL: psychology experiment building language.

^c^Lower values or a decrease over time indicate better functioning or improvement in the respective study endpoint.

^d^MRI: magnetic resonance imaging.

^e^fMRI: functional magnetic resonance imaging.

^f^Instrumented gait analysis using a figure of 8 walking path [108] at preferred walking speed using BTS G-WALK (BTS Bioengineering SpA, Garbagnate Milanese, Italy) inertial sensor attached with semielastic belt to the lower back of the participant.

^g^IADL: instrumental activities of daily living.

^h^vm-HRV: vagally-mediated heart rate variability.

^i^5 min resting vm-HRV measurement with heart rate monitor (Polar M430) and sensor (Polar H10) analyzed using Kubios HRV Premium (Kubios Oy, Kuopio, Finland, version 3.4) [118].

#### Primary Outcome

The German version of the quick mild cognitive impairment (Qmci) screen will be used to assess global cognitive functioning [96,99]. The Qmci has been validated against the standardized Alzheimer’s Disease Assessment Scale-Cognitive Subscale (ADAS-cog) [96,119], which is considered the gold standard for assessing the efficacy of antidementia treatments [120-122]. The Qmci was shown to “correlate strongly, significantly and correspondingly over time to the standardized ADAS-cog and that both are equally sensitive with similar responsiveness to deterioration over time” [119], “suggesting that the Qmci could be substituted for a more detailed neuropsychological instrument in clinical trials” [96,119]. Furthermore, it is accurate in differentiating mNCD from normal cognition and MNCD [119]. In this regard, it has also been externally validated and has shown a higher level of accuracy, sensitivity, and specificity than commonly used tests such as the (Standardised) Mini Mental State Exam ([S]MMSE) and the Montreal Cognitive Assessment for detecting cognitive impairment (MCI and dementia) [123]. In comparison to the (S)MMSE and Montreal Cognitive Assessment, the Qmci includes a more detailed scoring system and a logical memory task that allows the Qmci to detect more subtle cognitive abnormalities and avoid ceiling effects [123]. Qmci was scored as the point rate out of a maximum score of 100. It consists of 6 subtests: orientation (10 points), registration (5 points), clock drawing (15 points), delayed recall (20 points), verbal fluency (20 points), and logical memory (30 points) [99,124]. Qmci will be administered and evaluated according to published guidelines [99].

To the best of our knowledge, the smallest unit of clinically meaningful change has not yet been determined for the Qmci. However, changes in Qmci scores were very similar to changes in standardized ADAS-cog scores. Longitudinal data of more than 360 patients with m-MNCD were analyzed for responsiveness of the Qmci and the standardized ADAS-cog [125] by calculating standardized response mean from baseline to scores obtained at 1, 3, 6, 9, and 12 months. The mean change between months 1 and 12 was 5 points (SD 7.56) for the standardized ADAS-cog scores, and 5.41 points (SD 10.02) for the Qmci. The paired-samples *t* test showed no statistically significant difference in standardized response means for standardized ADAS-cog and Qmci (t_357_=0.32; *P*=.75) [119]. Therefore, it is anticipated that the smallest units of clinically meaningful changes between these 2 measures are similar. For the standardized ADAS-cog, the minimal clinically relevant change is estimated to be 3 points for individuals with mNCD compared with ≥4 points based on previous recommendations made by a consensus committee of the Food and Drug Administration for patients in more advanced stages [126,127]. Therefore, it is assumed that a change of ≥3 points in the Qmci score can be regarded as a clinically meaningful change.

#### Secondary Outcomes

##### Learning and Memory

Learning and memory will be assessed using the German version of the subtests “logical memory” of the Wechsler Memory Scale—fourth edition (WMS-IV-LM) [100,101] and a computerized version of the digit span forward (DSF) test (psychology experiment building language [PEBL; PEBL-DSF]) [102-104].

The WMS-IV-LM measures auditory verbal contextual learning and memory with excellent reliability and validity [101]. The validated older adults battery (aged 65 years or older) of the German version of the WMS-IV-LM [100,101,128] will be used for all participants. The test will be instructed, conducted, and evaluated according to the standardized administration and scoring manual [100]. During the 20 to 30 minutes retention phase, unrelated assessments (eg, gait analysis, questionnaires) will be performed that do not interfere with memory.

The PEBL-DSF test assesses immediate recall and will be executed using the PEBL Test battery software [version 2.1 (2), with default settings] [102-104]. Participants were required to remember and repeat the digit sequences presented on the screen. Span length covers 2 to a maximum of 8 digits. For each digit span, 2 trials will be presented before increasing the sequence length (in case at least one of the 2 trials is completed correctly). For every correct replication of a digit sequence, 1 point will be scored, summing up to a total point score. In addition, the length of the longest correctly repeated digit sequence will be recorded as the maximum span. Instructions will be presented on the screen and will be explained verbally to each participant before starting the test.

##### Complex Attention

Complex attention will be assessed using a computerized version of the Trail Making Test—Part A (PEBL-TMT-A) [102,104] and the subtest “Go-NoGo” of the Test of Attentional Performance (test of attentional performance [TAP] Go-NoGo) [105].

The TMT-A is a valid and reliable neuropsychological test for assessing psychomotor processing speed and visuo-perceptual abilities [129-134]. A computerized version of the TMT-A PEBL Test battery software [version 2.1 (2), with default settings] will be used [102,104,135]. Participants will be verbally instructed, and a short practice session will be conducted before starting the test. The completion time will be limited to 300 seconds. Completion times (seconds; including time for error correction) and the number of errors will be measured.

The TAP (version 2.3.1, PSYTEST, Psychologische Testsysteme, Herzogenrath, Germany) is a valid and reliable computerized test battery to assess various attentional and executive functions [105,136], with norm values for healthy older adults provided by the supplier [105,137]. The TAP Go-NoGo will be used to assess selective attention and inhibition. The test form “1 of 2” will be instructed, conducted and evaluated according to the standardized protocol of the manufacturer. The median reaction time and number of errors will be measured [105].

##### Executive Function

Executive function will be assessed considering planning (ie, using the HOTAP picture-sorting test part A [106]), working memory (ie, using a computerized version of the Digit Span Backward test; PEBL Digit Span Backward [PEBL-DSB]) [102-104], and cognitive flexibility (ie, using a computerized version of the Trail Making Test-Part B [PEBL-TMT-B] [102,104]).

HOTAP picture-sorting test part A [106] will be used to measure planning ability. A set of photo cards containing actions typical of everyday life (eg, making coffee, washing clothes, and grocery shopping) will be presented. Participants will be verbally instructed to sort photo cards on which the individual substeps of these typical everyday actions are depicted. The test will be conducted according to the manufacturer’s standardized protocol. The outcome variable is a combination score calculated as the sum of points divided by the time needed to arrange the cards [106].

The PEBL Digit Span Backward (PEBL-DSB) [102-104] test will be used to assess the short-term working memory capacity. It will be instructed, administered, and scored identical to the PEBL-DSF, but participants will have to remember and repeat the digit sequences in reverse order.

The TMT-B is a valid and reliable neuropsychological test for assessing cognitive flexibility [129-134]. It consists of 25 randomly allocated circles distributed over a sheet of paper. A computerized version of the TMT-A (PEBL Test battery software [version 2.1 (2), with default settings]) will be used [102,104,135]. It will be instructed, administered, and scored identical to the PEBL-TMT-A.

##### Visuospatial Skills

Visuospatial skills will be tested using a computerized version of the classic Shepard and Metzler mental rotation task [138]. The PEBL-Mental Rotation Task (PEBL-MRT) will be executed using PEBL Test battery software [version 2.1 (2), with default settings] [102,104,107]. Instructions will be presented on the screen and will be explained verbally to each participant before starting the task. Pairs of differently rotated 2D polygons will be presented simultaneously on the screen. Participants need to decide as quickly as possible whether the 2 presented objects are identical (ie, pressing <Lshift> on the keyboard) or different (ie, pressing <Rshift> on the keyboard). Median reaction time of correct answered trials as well as performance (number of correct answered trials) are an indicator for mental rotation ability [107,138]. Trials with reaction times less than 0.2 seconds or greater than 13 seconds will be excluded from the data analysis [107].

##### Brain Structure and Function: Data Acquisition

Brain structure and function will be evaluated by MRI using a 3.0 Tesla Philips whole-body scanner (Philips Medical Systems, Best, and Netherlands) to explore possible underlying neural changes of training in relation to adaptations in cognitive performance. Only participants having no contraindications to MRI (ie, any MRI-incompatible metallic parts within the body, metallic or electronic implants [eg, heart pacemaker, brain pacemaker, and cochlear implants], and strong claustrophobia) will be measured. During measurements (duration=approximately 35 min), participants will lay comfortably in the MRI scanner and will be asked to avoid head movements. Data will be collected according to the Canadian Dementia Imaging Protocol (CDIP) [139] for comparison with other studies. The CDIP was developed to harmonize MRI acquisitions in the context of studying primary and secondary causes of morbidity of neurodegeneration in a wide range of neurological pathologies related to aging [139]. First, the following parts of the core CDIP will be applied: anatomical imaging (1.) and connectivity and functional imaging (2. – 3.) [139]:

a 3D isotropic t1-weighted (*t*_1_w) scan (duration=6.5 minutes) for assessing fine anatomical detail and brain atrophy (voxel size=1.0×1.0×1.0 mm^3^) with an acceleration factor of 2 (TFE-Sense: 2); diffusion tensor imaging (DTI; duration=6 minutes) for assessment of white matter microstructural integrity and connectivity, with resolution 2.0×2.0×2.0 mm^3^, a minimum of 30 uniformly distributed directions with b=1000 second/mm^2^, (EPI-Sense 2-32 directions; we use the vendor-provided directions set), and an acceleration factor of 2; anda resting state fMRI (duration=9 minutes) for assessment of functional networks and pathways using a T*_2_-weighted blood oxygen level-dependent-sensitive sequence, with resolution of 3.5×3.5×3.5 mm^3^, repetition time=2110 milliseconds, 300 volumes over time, and slice order=ascending.

During resting-state fMRI data acquisition, participants will be asked to fixate on a cross displayed on the screen. At the end of this scan, participants must respond to written instructions by button press to check whether they were awake during the measurement.

In addition, task-based (event-related) fMRI measured with an episodic memory task (face-occupation matching task; duration: approximately 10 min) will be conducted. The face-occupation matching task was described in [140] and has been used in fMRI [141]. It was shown to robustly activate the hippocampus bilaterally and provide a differential signal for correct and incorrect trials [141]. The task was adapted specifically for older adults with mNCD [142] and will be run in PsychoPy (version 3.2.4) [143]. It includes 6 rounds, each containing (1) an encoding phase, (2) a retention phase, and (3) a retrieval phase including a cued recall task and a recognition task (see Figure 3 for an overview).

During the *encoding* phase, 5 face-occupation pairs will be presented in each round in a randomized order. A total of 30 face-occupation pairs (15 different face-occupation combinations) will be presented (Figure 3). Photographs of unfamiliar faces of older adults with neutral expressions were derived from the FACES database [144] and will be equally balanced over sex. Each face-occupation pair will be shown for 3.5 seconds. To ensure that participants view both faces and occupations, they will be asked to indicate whether each respective occupation “suits” (ie, pressing a button with their right index finger) or does not suit the presented face (ie, pressing a button with their right middle finger).

During the *retention* phase, 5 silhouettes will be presented in randomized order in each round. A total of 30 silhouettes will be presented. Each silhouette will be shown for 3.5 seconds. Participants will be asked to indicate by button press whether each silhouette corresponds to a woman (pressing a button with their right index finger) or a man (pressing a button with their right middle finger).

In the *retrieval* phase, a cued-recall task will be performed followed by a recognition task. In the cued recall task, participants will be asked to decide which of 2 educational degrees (ie, study [pressing a button with their right index finger] or apprenticeship [pressing a button with their right middle finger]) the previously encoded occupation of the person matched. In the recognition task, participants will have to decide between correct and distractor occupation via a button press (right index finger or right middle finger). For both the tasks, the response window will be 3.5 seconds. The photographs will be presented in the same order as those in the encoding phase.

The same recording parameters as in resting-state fMRI will be used. There are 4 alternative task conditions (ie, other face-occupation pairs). The task condition will be randomly allocated using random.org [145], while ensuring that 2 different conditions are used in the pre- and postintervention measurements for each participant.

**Figure 3 figure3:**
[figure not shown]
Graphical overview of the episodic memory task (face-occupation matching task).

##### Brain Structure and Function: Data Analysis

Processing and volumetric segmentation of *t*_1_w morphological data is performed using the longitudinal pipeline of the FreeSurfer software package (version 7.2.0 or newer with default parameters) [146,147], as described in [148]. Gray matter volumes and WMVs are determined for the following key regions of interest (ROIs): total brain (ie, total brain volume without ventricles [brainsegvolnotvent] from the aseg file), hippocampus, dorsolateral prefrontal cortex, PFC, and anterior cingulate cortex (ACC). Similar to Anderson-Hanley et al [77,78], we will combine the following regions to obtain the defined key ROIs of the dorsolateral prefrontal cortex, PFC, and ACC, because these are not directly extracted using the FreeSurfer software package: dlPFC=frontal middle gyrus and sulcus from the Destrieux et al [149] atlas; ACC=rostral and caudal anterior cingulate cortices from the Desikan et al [150] atlas; PFC=ACC+medial orbitofrontal and transverse frontopolar regions [151].

DTI data will be processed using the TractoFlow pipeline [152,153], a diffusion MRI tractography processing pipeline based on Nextflow [154] and Singularity [155], for human brain tractography reconstruction. In patients with m-MNCD, DTI abnormalities are concentrated in the posterior regions, whereas the most reported regions of DTI alterations are the temporal lobes, with a particular emphasis on the parahippocampal white matter and posterior cingulum [156,157]. Therefore, MD and FA will be calculated for the parahippocampal white matter and posterior cingulum, defined as key ROIs for this study. In addition, tract-based spatial statistical analysis will be performed to study white matter changes at voxel-to-voxel (whole-brain) levels. Tract-based spatial statistical analysis is based on a general linear model and will be performed using FSL’s randomization tool [158] with 5000 permutations to correct for multiple comparisons (*P*<.05, corrected). All results will include threshold-free cluster enhancement [159]. The threshold-free cluster enhancement correction method is somewhat similar to cluster-based thresholding but is generally more robust and avoids the need for an arbitrary initial cluster-forming threshold. Two contrasts will be computed at the individual and group levels, testing for positive and negative differences in FA and MD parameters pre- and postintervention. We will include age and sex as key covariates in the general linear model.

Data of *resting state and task-based fMRI* will be preprocessed to minimize data artifacts from thermal noise of MRI, system noise of the MR hardware, and subject-related noise resulting mostly from head motion [160]. The preprocessing steps will include slice time correction, motion correction, coregistration, and spatial smoothing (Gaussian kernel with 7 mm full width at half maximum) of the signal [161]. For functional connectivity (FC) analysis, preprocessed resting-state functional data will be analyzed using the latest release of the Functional Connectivity Toolbox (currently CONN 21a; [162,163]) in SPM12. The CONN utilizes a component-based noise correction method (CompCor) that increases selectivity and sensitivity and allows a higher degree of interscan reliability [164]. In addition to the described preprocessing steps, a band-pass filter (0.01-0.1 Hz) will be applied to remove linear drift artifacts and high-frequency noise. The CONN also accounts for outlier data points and movement time courses as nuisance regressors. The 6 motion parameters, WM and CSF, will be included as regressors of no interest, thereby reducing noise and signals that are unlikely to reflect neuronal activity related to FC. Age and sex will be included as key covariates of no interest. Significance was set at *P*<.05 with Family Wise Error-level correction for multiple comparisons (with *P*<.05 2-sided false-discovery rate correction) [163].

Bilateral hippocampal masks were selected as seeds from an Anatomical Automatic Labeling template [165]. Individual FC maps for the hippocampal seed will then be generated based on correlations between the mean signal time course within each seed region and the rest of the brain, similar to Suo et al 2016 [166], with the following selected key ROIs (ie, brain regions related to cognitive functioning, similar to Zhong et al [167]): precuneus or posterior cingulate cortex, medial prefrontal cortex, medial temporal lobe, angular gyrus, lateral temporal cortex, and medial, lateral, and inferior parietal cortex.

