### Objectives and Hypotheses

This study explores the effectiveness of the “Brain-IT” training in improving global cognitive functioning in older adults with mNCD. With this, we aim to obtain a sufficiently precise estimate of the treatment effect to minimize the sample size needed for a future full-scale RCT.

Null Hypothesis (H_0_0): In older adults with mNCD, the addition of the “Brain-IT” training to usual care has no significant effect on global cognitive functioning compared with usual care.Alternative Hypothesis (H_A_): In older adults with mNCD, the addition of the “Brain-IT” training to usual care results in differing effects on global cognitive functioning compared with usual care.

As secondary objectives, the effects of the “Brain-IT” training on (a) domain-specific cognitive functioning (ie, learning and memory, complex attention, executive function, and visuospatial skills), (b) brain structure and function, (c) spatiotemporal parameters of gait, (d) instrumental activities of daily living (IADL), and (e) psychosocial factors (ie, QoL [quality of life], and levels of depression, anxiety, and stress), and (f) cardiac vagal modulation (ie, resting vagally-mediated heart rate variability [vm-HRV]) in older adults with mNCD as compared with usual care will be explored. (B) Brain structure and function will be evaluated to explore the possible underlying neural changes in training in relation to adaptations in cognitive performance. The following hypotheses are formulated for the remaining outcomes:

Null Hypothesis (H_0_): In older adults with mNCD, the addition of the ‘Brain-IT’ training to usual care has no significant effect on (a) domain-specific cognitive functioning, (c) spatiotemporal parameters of gait, (d) IADL and (e) psychosocial factors (ie, QoL, and levels of depression, anxiety, stress), and (f) cardiac vagal modulation (resting vm-HRV) compared with usual care.Alternative Hypothesis (H_A_): In older adults with mNCD, the addition the “Brain-IT” training to usual care results in differing effects on (a) domain-specific cognitive functioning, (c) spatiotemporal parameters of gait, (d) IADL, (e) psychosocial factors (ie, QoL, and levels of depression, anxiety, and stress), and (f) cardiac vagal modulation (resting vm-HRV) compared with usual care.

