### Statistical Methods

Statistical analysis will be executed using R (The R Foundation), in line with RStudio (RStudio Inc). For demographics as well as training adherence and compliance, all collected data will be included (ie, including data of dropouts up to the time point of their withdrawal). For primary and all secondary outcomes, the data of all participants who completed pre- and postintervention measurements, regardless of protocol adherence, will be included in the statistical analyses. Questionnaire scores will be regarded as ordinal data. Data will be reported as mean (SD) values for continuous parametric data and median (IQR) values for continuous nonparametric data.

For all outcomes, descriptive statistics will be computed first. Normality distribution of data will be checked using the Shapiro-Wilk test. The level of significance will be set to *P*≤.05 (2-sided, uncorrected).

For all demographic variables, between-group differences (ie, intervention vs control) will be tested using an independent *t* test or Mann-Whitney *U* test in case the data are not normally distributed. For primary and secondary outcomes, the assumption of homogeneity of variance will be checked using Levene test. In case all assumptions for a 2-way analysis of covariance (ANCOVA) are met, effectiveness of the “Brain-IT” training will be analyzed using a two-way ANCOVA with the premeasurement value as covariate for the predicting group factor and the postmeasurement value as outcome variable [202]. If not all assumptions are met, the Quade nonparametric ANCOVA will be used. Because of the stratification by sex in the randomization process, no sex-specific statistical analysis will be computed. However, if there are relevant between-group differences in sex distribution or other demographic variables, these will be included in the statistical analyses as additional covariates. To determine whether the effects are substantive, partial eta-squared (η^2^_p_) effect sizes will be calculated for all primary and secondary outcomes. Effect sizes will be interpreted as small (0.01≤η^2^_p_<0.06), medium (0.06≤η^2^_p_<0.14), or large (η^2^_p_>0.14) [203].

Statistical analysis will be performed by PM after data collection is completed. As this is a small-scale RCT, no interim analysis will be performed.

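### The added whole-brain DTI analysis is written as a pre/post contrast without trial arm, and does not say how .05 is shared between its two directional tests

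*Protocol article*

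**What the plan says.** Objectives and Hypotheses states the secondary objectives, brain structure and function among them, as effects "in older adults with mNCD as compared with usual care will be explored". It formulates no null or alternative hypothesis for the imaging item.

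Brain Structure and Function: Data Analysis first defines MD and FA in two key white-matter regions. It then adds a separate analysis: "In addition, tract-based spatial statistical analysis will be performed to study white matter changes at voxel-to-voxel (whole-brain) levels". This analysis has its own general linear model and its own threshold, "with 5000 permutations to correct for multiple comparisons (*P*<.05, corrected". The contrasts are given in one sentence, which plans two of them, at both individual and group level, "testing for positive and negative differences in FA and MD parameters pre- and postintervention". The only model terms named are in the next: "We will include age and sex as key covariates in the general linear model".

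Statistical Methods analyses primary and secondary outcomes by ANCOVA of the post value on group with the pre value as covariate, or by Quade's method if assumptions fail. The significance level is .05, "2-sided, uncorrected". Table 2 lists MD and FA for the key regions only; the whole-brain analysis is not in it.

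For functional connectivity, the data analysis section sets significance at .05 "with Family Wise Error-level correction for multiple comparisons" and adds, in brackets, a two-sided false-discovery-rate correction, also at .05.

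**The concern.** A contrast of post against pre measures everything that changes over the 12 weeks: training, ageing, scanner drift and retest effects. Only the difference in change between the arms isolates what the training adds to usual care. A map that is significant in the intervention arm and not in the control arm does not show that the arms differ. If the whole-brain analysis is run as written, a change common to both arms could be reported as a white-matter effect of training.

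The second issue is the error rate. A permutation correction of this kind protects across voxels within one contrast. It does not by itself protect across two contrasts in opposite directions, and the text does not say whether .05 is the level of each contrast or of the pair.

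**Working it through.** **Step 1. Which contrast is described?**

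- The objective is a comparison with usual care (Objectives and Hypotheses).
- The quantity tested is a positive or negative pre/post difference in FA and MD (data analysis section).
- The same two contrasts are to be computed at the individual level as well as at group level. One participant belongs to one arm, so no between-arm contrast exists at the individual level. What both levels can share is pre against post.
- Age and sex are the named model terms. Arm is not named.

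The natural reading is therefore a time contrast. The ANCOVA in Statistical Methods does not repair it, because that model covers the listed outcomes and Table 2 contains only the regional FA and MD measures.

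**Step 2. What a time contrast does when training has no effect.** The settings below, other than 14 per arm (Sample Size), are assumptions for illustration: 100 voxels with correlation 0.5, a maximum-statistic permutation test with 500 permutations, both directions at .05, 800 simulated data sets. The table gives the share of data sets with at least one significant voxel in either direction.

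| Change common to both arms (assumed) | n = 14 (one arm) | n = 28 (arms pooled) |
|---|---|---|
| 0 | .111 | .091 |
| 0.2 SD | .211 | .365 |
| 0.5 SD | .735 | .943 |

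With no common change the rate is near .10, as two directional tests at .05 would give. It then rises with the common change and with n, although training does nothing.

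**Step 3. Sharing of the .05.** The stated figure is corrected P<.05, with no allocation to contrasts. Both readings were tried:

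- .05 per direction: bound 2 × .05 = .10. If independent, 1 − .95² = .0975. This does not match a two-sided .05.
- .025 per direction: bound 2 × .025 = .05. If independent, 1 − .975² = .049. This matches.

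A simulated between-arm test on change maps (14 per arm, same voxel settings, 1,500 data sets) gave .043 and .051 for the two directions at .05 each and .094 for either. At .025 each, either direction gave .047.

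Over FA and MD together, .05 per direction has a bound of 4 × .05 = .20 (.185 if independent), and .025 per direction has 4 × .025 = .10. Since the text does not say which level applies, whether the plan meets its own two-sided .05 cannot be determined.

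**Step 4. Connectivity.** Family-wise error and false-discovery rate control different quantities. The section gives both at .05 without assigning either to a level, while Statistical Methods calls the trial's level uncorrected and connectivity is a listed secondary outcome. Three statements on error control therefore apply to one outcome.

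**The case against.** The strongest reply is that the sentence is compressed, not wrong. Group level may mean the trial arms, or a second-level analysis comparing pre/post differences between arms, and an article may leave a design matrix to the full protocol. The text does not exclude this. But the article does state the contrasts and the covariates; pairing the group level with the individual level points to time, and arm is absent from the model description. A plan that means a between-arm contrast should say so.

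Second, .05 per contrast is not in the text. That stands: the 10% per metric and 20% over both metrics are upper bounds conditional on one reading. The doubling across FA and MD is also no departure from the plan, which openly leaves multiplicity across outcomes uncorrected.

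Third, imaging is exploratory, has no formal hypothesis, and the Limitations section expects the analyses to be underpowered. That stands too and limits the weight of the point. It does not make a time contrast an answer to a between-arm question.

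A reader might infer that imaging inference as a whole does not test the training effect at 5%. The documents do not support that. Regional volumes, regional MD and FA, and hippocampal-seed connectivity are secondary outcomes in Table 2, and Statistical Methods tests arm on each of them, adjusted for baseline, at a two-sided .05. Nor does the connectivity paragraph show a failure to compare arms: it writes no pre/post contrast, its false-discovery-rate statement is two-sided, and the two corrections may belong to different levels of the analysis.

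**Conclusion.** The point holds for the additional whole-brain FA and MD analysis only. On its natural reading that analysis tests change over time and not the difference in change between arms, so it cannot separate training from whatever else moves both arms. The simulated 21% to 94% false findings rest on assumed common changes of 0.2 to 0.5 SD and a simplified voxel structure. They show the direction and possible scale, not a forecast for this trial.

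The error rate for the two directions is unspecified. It is up to 10% two-sided per metric if .05 is applied to each contrast, and 5% if .025 is.

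The primary outcome and the imaging outcomes in Table 2 are unaffected by these two points. The wording on family-wise error and false-discovery rate is a minor ambiguity to clear up, not a demonstrated error.

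**What to change.** In the whole-brain paragraph, state that the permutation model is run on each participant's post-minus-pre FA and MD maps, with arm as the tested regressor and age and sex as nuisance regressors. Name the two contrasts, intervention above control and control above intervention, each at corrected P<.025, so that the pair uses a two-sided .05 per metric. State that within-arm pre/post maps are reported descriptively, without inference.

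In the connectivity paragraph, say which of family-wise error and false-discovery rate applies at which level, and reconcile this with the uncorrected level in Statistical Methods.

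The cost is a change of wording and of the design matrix. No further scans are needed. The price is a slightly stricter threshold for each directional map, and so somewhat less power in an analysis that is already exploratory.
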